**Figure 1. f1:**
[figure not shown]
Activity chart. Study design flow chart illustrating the participant activity. Participants were screened and assessed for eligibility, then randomized into two groups: Group A (Control) and Group B (Trial). Assessments will be conducted in baseline, 30, 60, and 90 days during the 3-month intervention period, with a follow-up of 180 days.

**Table 4. T4:** Participant timeline.

Parameter	Instrument	Screening	Baseline	30 days	60 days	90 days (End Tx)	180 days (Follow-up)
Informed consent	Consent form	+					
Demographic and medical history	Case report form	+					
Clinical examination	As per need	+	+				
Assessment of ADR	ADR reporting form			+	+	+	+
Assessment of drug compliance	Compliance chart			+	+	+	
Issue of trial drugs	Trial drug kit		+	+	+		
Visual acuity (distant & near)	ETDRS LogMAR Chart	+	+	+	+	+	+
Automated VF testing (30–2 SITA standard)	ZEISS Humphrey Field Analyzer 3 (HFA)	+	+	+	+	+	+
Retinal Nerve Fiber Layer (RNFL) Thickness	ZEISS CIRRUS HD-OCT	+	+	+	+	+	+
Intraocular Pressure (IOP)	Goldmann Applanation Tonometer/Non-Contact Tonometer (NCT)	+	+	+	+	+	+
Central Corneal Thickness (CCT)	TOPCON Pachymeter/ZEISS CIRRUS HD-OCT	+	+	+	+	+	+
CBC with ESR, FBS, KFT, LFT	Standard Clinical Laboratory Tests		+	–	–	+	–

ADR – adverse drug reaction, CBC – complete blood count, CCT – central corneal thickness, ETDRS – early treatment diabetic retinopathy study, ESR – erythrocyte sedimentation rate, FBS – fasting blood sugar, HFA – humphrey field analyzer, IOP – intraocular pressure, KFT – kidney function test, LFT – liver function test, LogMAR – logarithm of the minimum angle of resolution, NCT – non-contact tonometer, OCT – optical coherence tomography, RNFL – retinal nerve fiber layer, VF – visual field.

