### Blinding

This is an open-label trial. Neither participants nor investigators are blinded due to the nature of the intervention.

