### Criteria for discontinuing or modifying allocated interventions

If a participant experiences serious adverse events or shows clinically significant deterioration that appears linked to the RF or SP eye drops, the intervention may be paused or discontinued at the investigator’s discretion. Participants retain the right to withdraw voluntarily at any time. In cases where IOP or optic nerve parameters substantially worsen, or if an alternative therapy becomes necessary for emergent ophthalmic conditions, the intervention may also be modified or halted. If a participant becomes pregnant during the study, the intervention will be discontinued due to insufficient safety data in this population. All such modifications and discontinuations will be recorded in the case report forms (CRFs).

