### Assessment and data collection

The principal investigator (PI) oversees all data management activities, including data entry verification, cleaning, codebook maintenance, and data security. Participants will undergo baseline and follow-up evaluations at 30, 60, and 90 days (end of treatment), as well as at 180 days (90-day follow-up). Specific assessments include visual acuity (LogMAR), VF testing (perimetry), OCT RNFL thickness, IOP, CCT, and laboratory investigations (CBC, ESR, FBS, KFT, LFT), as outlined in
Table 3. The overall schedule is detailed in
Figure 1 and
Table 4. Instruments such as the Humphrey Field Analyzer and OCT are recognized as valid and reliable for glaucoma diagnostics. All personnel responsible for VF tests, OCT scans, or tonometry received protocol-specific training. CRFs and compliance charts are securely stored at the coordinating center, and standardized operating procedures (SOPs) are employed throughout the data entry process to maintain consistency and accuracy.

**Table 3. T3:** Details of parameter assessment.

S. No	Parameters		Unit	Instrument
1.	Visual acuity - Distant		Number in decimals	ETDRS LogMAR chart
				Landolt C LogMAR chart
				Tumbling E LogMAR chart
2.	Visual acuity - Near		Number in decimals	ETDRS LogMAR near vision chart
3.	Best corrected visual acuity		Number in decimals	ETDRS LogMAR chart
4.	Perimetry	GHT	Outside normal limits-1 Within normal limits-0	ZEISS Humphrey field analyser 3 (HFA), Mark III SITA standard 30–2
		VFI24-2	In %	
		MD30-2	dB	
		PSD30-2	dB	
5.	OCT- OPTIC DISC CUBE 200x200	Average RNFL Thickness	μm	ZEISS CIRRUS HD - Optical Coherence Tomography (OCT)
		RNFL Symmetry	%	
		Rim Area	mm ^2^	
		Disc Area	mm ^2^	
		Average C/D Ratio	Number in decimals	
		Vertical C/D Ratio	Number in decimals	
		Cup Volume	mm ^3^	
6.	IOP measurement		mm of Hg	Goldmann Applanation tonometer, TOPCON Non-Contact Tonometer (NCT), Adjusted value
7.	Central corneal thickness (CCT)		mm	TOPCON Pachymeter/ZEISS CIRRUS HD - OCT

CCT – central corneal thickness, C/D Ratio – cup-to-disc ratio, ETDRS – early treatment diabetic retinopathy study, GHT – glaucoma hemifield test, IOP – intraocular pressure, LogMAR – logarithm of the minimum angle of resolution, MD – mean deviation, NCT – non-contact tonometer, OCT – optical coherence tomography, PSD – pattern standard deviation, RNFL – retinal nerve fiber layer, VFI – visual field index.

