### Adverse events reporting

Any adverse events arising during the clinical trial will be promptly reported to the National Pharmacovigilance Coordination Centre (NPvCC), AIIA, New Delhi, India (
https://www.ayushsuraksha.com). If any adverse event is determined to be related to the trial interventions, appropriate ancillary care and management will be provided to the affected participants as per protocol guidelines.

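### Table 4 schedules only adverse drug reactions while the safety section covers all adverse events; in an open-label trial the two should be aligned

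*Protocol article*

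**What the plan says.** Two places in the protocol article describe how harms are handled, and they use different terms.

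- **Table 4 (Participant timeline).** There is one harms row, "Assessment of ADR", with the "ADR reporting form" as its instrument. It is ticked at days 30, 60, 90 and 180. The table notes give "ADR – adverse drug reaction".
- **Adverse events reporting.** The commitment is wider: "Any adverse events arising during the clinical trial will be promptly reported to the National Pharmacovigilance Coordination Centre (NPvCC"). It has no limit by arm or by suspected cause. The next sentence begins "If any adverse event is determined to be related to the trial interventions", so here relatedness is settled after an event has been identified.

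Two further sections bear on the point. Under Blinding: "Neither participants nor investigators are blinded due to the nature of the intervention". Under the criteria for discontinuing or modifying interventions, one trigger is that a participant "shows clinically significant deterioration that appears linked to the RF or SP eye drops", which also depends on attribution.

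**The concern.** An adverse event is any untoward occurrence. An adverse drug reaction is one that somebody already believes a drug caused. A form for reactions therefore filters on causality before anything is recorded, whereas a form for events records first and judges causality later. The protocol's safety section implies the second order and its visit schedule the first.

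The order matters more here than in a blinded trial. Whoever judges causality knows whether the participant is taking the Rasayana Formulation and the Shigru Pallava drops. A headache or a red eye may prompt suspicion in one arm and be passed over in the other, in either direction. The control arm's background rate of such events is the natural yardstick for a multi-component add-on, and it is useful only if both arms are asked and recorded alike. Decisions to pause treatment, and the early termination allowed for under Interim analyses, also turn partly on whether events appear linked to the intervention. That makes an unfiltered record in both arms worth having.

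**Working it through.** The protocol states no adverse event rate, safety hypothesis or safety sample size, so there is no figure to reproduce. The check is a comparison of the text.

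**1. Does another scheduled item pick up general symptoms?** The rows of Table 4 after baseline are:
- ADR assessment: days 30, 60, 90 and 180.
- Compliance: days 30, 60 and 90.
- Issue of trial drugs: days 30 and 60.
- Visual acuity, visual field, RNFL thickness, IOP and CCT: every visit.
- Laboratory panel: day 90.

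Clinical examination is ticked only at screening and baseline. For symptoms, the ADR row is the only scheduled enquiry.

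**2. Does the safety section settle the matter?** It sets a duty to report any adverse event, and it puts the event first and relatedness second. As printed, it does not say that the Table 4 form is to be read that widely. The two passages are compatible only if the ADR form is broader than its name.

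**3. Is the row confined to one arm?** No. Table 4 marks no row by arm, and the text says of participants generally: "Participants will undergo baseline and follow-up evaluations at 30, 60, and 90 days". That silence proves little either way, because the trial drug row is unmarked too.

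**4. Can reactions arise in the control arm?** Yes. Table 1 and the Comparator section give Group A topical or oral anti-glaucoma drugs.

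**5. What is outside the problem?** Laboratory values are measured whatever anyone suspects, and Statistical methods plans unpaired t-tests between groups for them. The ocular measures are scheduled for all participants.

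**6. What would drive a bias?** Let *p* be the true event rate, the same in both arms, and let *a*(A) and *a*(B) be the proportions of events called reactions in each arm. If only reactions are recorded, the expected recorded difference is

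*p* × [*a*(B) − *a*(A)].

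It is zero when attribution is equal, although both arms are then under-counted whenever *a* is below 1. It is positive or negative otherwise. The document gives none of the three quantities, so the difference has neither a known size nor a known sign.

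For scale only: with 30 and 20 participants planned, classifying one participant's event differently moves an arm's rate by 1/30 = 3.3 percentage points in Group B or 1/20 = 5 percentage points in Group A.

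**The case against.** The strongest reply is that this is a loose table label. The section devoted to safety covers all events in both arms and assesses relatedness afterwards, and a row title should not override it. The form itself is not shown, and a journal article may properly leave its contents and the method of asking to the full protocol. The discontinuation criterion is also weak support: it governs stopping the add-on products, so naming them is natural, and it does not decide what is recorded.

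Much of this stands. No passage says outright that causality is judged before recording, and the form may be wider than its title. What remains is that two passages on the page disagree, and the narrower one is the schedule that staff work from.

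A reader might go further and infer that control-arm harms will go largely unrecorded, or that the arms cannot be compared on safety at all. The document supports neither. The ADR row is not restricted to Group B, Group A takes drugs that can cause reactions, laboratory values have a planned between-group test, and ocular measures are taken in everyone. Nor is a particular false excess or deficit of events derivable, since any such figure depends entirely on the attribution rates one chooses to assume.

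**Conclusion.** The point holds as a minor inconsistency. The schedule names reactions and the safety section names all events. Under open-label conditions, the literal reading of the schedule lets a judgement made with the arm known decide which clinical events enter the record. The consequence is a risk of unequal ascertainment confined to symptom-type events. Its size and direction cannot be estimated from the document.

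The conclusion assumes that the form is used as its name suggests. If it already captures every event whatever the suspected cause, the fault is one of labelling only.

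**What to change.** Reconcile Table 4 with the section on adverse events reporting:

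- Rename the row *Assessment of adverse events (all, regardless of suspected cause)*, with the same question put in the same way in both arms at days 30, 60, 90 and 180.
- Record the event first and causality afterwards, as a separate field. The ADR form can be kept for the subset judged related.
- Report all-cause adverse events by arm.

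The cost is one table row and, if the present form is narrower than this, one case report form page. No visit, test or member of staff is added. The downside is more minor events to write down. Because recruitment is under way, the change is best made soon: events not recorded at the time may be hard to recover. If the existing form already collects all events, correcting the label is enough.

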### Data management

Data entry is conducted by PI using verification procedures, with all information recorded in a password-protected electronic database. Each participant is assigned a unique study ID, and direct identifiers are stored separately from the clinical dataset. The electronic database is accessible only to authorized personnel, and all physical documents (CRFs) are kept in locked cabinets at the study site. To ensure data quality, built-in range checks and validation rules automatically flag any out-of-range or inconsistent entries (Microsoft® Excel® for Microsoft 365 MSO (Version 2503 Build 16.0.18623.20076) 64-bit).

### Statistical methods

Within each group, repeated-measures analysis of variance (RM-ANOVA) or a suitable post-hoc test will be employed to analyze continuous variables, including LogMAR acuity, visual field index (VFI), MD, pattern standard deviation (PSD), RNFL thickness, IOP, and central corneal thickness (CCT) depending on the normality of distribution. Between-group comparisons will be performed using the unpaired t-test or its nonparametric alternatives as needed. Laboratory parameters such as complete blood count (CBC), erythrocyte sedimentation rate (ESR), fasting blood sugar (FBS), kidney function test (KFT), and liver function test (LFT) will be assessed via paired t-tests for within-group changes and unpaired t-tests for between-group differences. All statistical analyses will be conducted using IBM SPSS Statistics (Version 29) or later.

The primary analysis follows the intention-to-treat (ITT) principle, incorporating all randomized participants who have received at least one dose of the allocated intervention. Missing data, when deemed missing at random, may be addressed using multiple imputation based on observed participant characteristics. A per-protocol (PP) analysis will also be performed among participants who strictly adhere to the intervention, serving as a sensitivity assessment to confirm the robustness of the results.

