## Protocol

### Objectives

**Primary objective:** To compare the neuroprotective activity of a RF (2.5 g administered twice a day) as an add-on therapy to the standard of care at 30, 60, and 90 days in patients with POAG.

**Secondary objective:** To compare the effect of SP eye drops [1 drop (0.05 mL)/eye] four times a day on IOP when used as an add-on therapy to the standard of care at 30, 60, and 90 days in patients with POAG.

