### Study design

This is an exploratory, open-label, two-arm, parallel-group randomized controlled trial with a 2:3 (control: intervention) allocation ratio. The total study duration for each participant is 180 days (90 days of intervention followed by 90 days of follow-up).

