### Sample size

This is an exploratory study; no prior data exists for neuroprotection as the primary outcome in POAG with Ayurveda intervention. A minimum of 50 participants will be enrolled in total, with 30 participants assigned to the intervention group and 20 participants assigned to the control group.

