### Outcomes

The primary outcome is the neuroprotective activity of the study interventions, measured by changes in optic nerve function, including alterations in VF indices (MD, PSD, VFI) and RNFL thickness. The secondary outcome comprises IOP changes assessed via tonometry, evaluating the potential ocular hypotensive effect of SP eye drops.

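### The repeated-measures analysis tests change within each arm only, and the arm comparison is an unpaired t-test with no baseline covariate and no fixed visit or scale

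*Protocol article*

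**What the plan says.** The Objectives section of the protocol article sets a comparison of arms for the three on-treatment visits (days 30, 60, 90): "To compare the neuroprotective activity of a RF (2.5 g administered twice a day) as an add-on therapy to the standard of care". The Outcomes section defines the primary outcome as "measured by changes in optic nerve function, including alterations in VF indices (MD, PSD, VFI) and RNFL thickness".

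The Statistical methods section assigns two kinds of analysis to these outcomes:

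- **Within arms:** "Within each group, repeated-measures analysis of variance (RM-ANOVA) or a suitable post-hoc test will be employed to analyze continuous variables". The choice between the two is said to depend on normality.
- **Between arms:** "Between-group comparisons will be performed using the unpaired t-test or its nonparametric alternatives as needed".

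No arm-by-visit term, joint longitudinal model or baseline covariate is named. The between-arm sentence does not say which visit is tested, or whether the t-test is run on raw follow-up values or on change. Table 4 shows visual field testing, RNFL thickness and IOP measured at screening, baseline, 30, 60, 90 and 180 days. The planned arms are 30 intervention and 20 control, under a 2:3 allocation.

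**The concern.** The analysis that uses the repeated visits does not compare the arms, and the analysis that compares the arms is the simplest available and is not fully fixed.

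Within-arm change mixes any add-on effect with everything else that moves both arms, such as standard care (which both arms receive), learning on repeated perimetry and regression to the mean. A significant change in one arm and not in the other is not a test of the difference between them. With 30 against 20 patients, the larger arm reaches significance more often for the same true change. That asymmetry favours the add-on.

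The t-test does answer the objective. However, baseline is collected for every outcome and is not used as a covariate, so with 50 patients some precision is left unused. How much depends on a choice that the plan leaves open.

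The within-arm sentence also has a technical error. A post-hoc test follows an omnibus test; it is not the substitute for RM-ANOVA when data are non-normal.

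**Working it through.** The protocol states no effect size, SD, alpha or power, so there is no power figure to reproduce. The only arithmetic to confirm is 20 + 30 = 50 and 20:30 = 2:3; both are consistent.

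**Inputs from the protocol:** n = 20 (control) and n = 30 (intervention); outcomes measured at baseline and at each follow-up visit.

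**Assumptions:** two-sided alpha 0.05; baseline-to-follow-up correlation r from 0.6 to 0.8 for the main figures, with 0.3 and 0.9 as outer values; equal SD at both times.

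**1. Precision of the arm comparison.** With the variance of a follow-up value set to 1, the relative variances of the arm difference are:

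- follow-up value only: 1
- change from baseline: 2(1 − r)
- baseline-adjusted (ANCOVA): 1 − r², ignoring the small cost of estimating the slope

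| r | Follow-up only | Change | Adjusted | Cut against change | Cut against follow-up only |
|---|---|---|---|---|---|
| 0.6 | 1 | 0.80 | 0.64 | 1 − 0.64/0.80 = 20% | 36% |
| 0.8 | 1 | 0.40 | 0.36 | 1 − 0.36/0.40 = 10% | 64% |
| 0.9 | 1 | 0.20 | 0.19 | 1 − 0.19/0.20 = 5% | 81% |

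To express this as power, take a true difference of 0.5 SD. The standard error is √(v(1/20 + 1/30)), where v is the relative variance. With v = 1 it is 0.289, so 0.5/0.289 = 1.73. By the normal approximation, power is Φ(0.5/SE − 1.96):

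| r | Follow-up only | Change | Adjusted |
|---|---|---|---|
| 0.3 | 41% | 31% | 44% |
| 0.7 | 41% | 61% | 68% |
| 0.9 | 41% | 97% | 98% |

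**2. Within-arm tests with no add-on effect.** Suppose both arms have the same true change d, in units of the SD of change, and each arm is tested alone with a one-sample t-test. At d = 0.5 the noncentral t gives power 0.754 for n = 30 and 0.565 for n = 20. The arms are independent, so:

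- only the intervention arm significant: 0.754 × (1 − 0.565) = 0.328, about 33%
- only the control arm significant: 0.565 × (1 − 0.754) = 0.139, about 14%

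The first figure depends on d: 16% at 0.2, 27% at 0.3 and 7.5% at 0.8. Equal arms of 25 would give about 22% each way at d = 0.5, so unequal allocation adds about 11 points in favour of the intervention arm.

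A simulation of the planned kind of analysis agrees. It ran separate RM-ANOVAs at baseline, 30, 60 and 90 days with 3,000 replicates per scenario, compound symmetry and an identical linear change in both arms. At r = 0.7 and a common change of 0.3 to 0.4 SD (here the SD of a single measurement), exactly one arm was significant in 46% to 50% of trials, and only the intervention arm in 30% to 34%. In the same scenarios the unpaired t-test on change rejected in 4.5% to 5.4% of trials, so it holds its level.

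**3. Missed visits.** Standard RM-ANOVA uses participants with all visits. At an assumed 5% independent missingness per visit, complete cases are 0.95⁴ = 0.815 over four post-baseline visits (about 9 of 50 lost), or 0.95³ = 0.857 over the three visits in the objectives (about 7 of 50 lost).

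**The case against.** The strongest reply is that a direct test of the add-on effect is already planned. Randomization makes an unpaired t-test unbiased without covariates, and one at each of 30, 60 and 90 days answers the objective as written. This stands. A reader might infer that the plan never tests the add-on effect; the between-arm sentence and the simulated 5% level show otherwise.

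A reader might also infer that baseline data are discarded. The documents do not support that. The outcomes are defined as changes, so a t-test on change is the natural reading, and a within-arm RM-ANOVA presumably includes the baseline visit. On that reading the loss is the smaller figure (20% to 10% of variance at r = 0.6 to 0.8). The 36% to 64% applies only if raw follow-up values are compared, which the plan neither states nor excludes.

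Nor is losing 9 of 50 participants a planned consequence. The missingness rate is assumed, the section permits multiple imputation, and the retention plan tries to obtain assessments after discontinuation. The imputation wording is optional, so the loss remains possible.

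Finally, nothing in the protocol says that a significant result in one arm only will be read as neuroprotection. At about 33% for one chosen effect size, it would be wrong to call that pattern likely. The study is also declared exploratory. That lowers the stakes, but within-arm p-values still do not become evidence about a difference between arms.

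The visit, scale and covariates might be set in a fuller document. The separate within-arm RM-ANOVA and the unpaired t-test, however, are methods that this article itself names.

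**Conclusion.** The point holds as a matter of precision and interpretation; it is not a claim that the arm comparison is invalid. The stated methods leave 10% to 20% of variance unused if the t-test is on change, and 36% to 64% if it is on follow-up values, at r = 0.6 to 0.8. The within-arm analysis cannot carry an add-on claim: with no add-on effect it singles out the intervention arm in about a third of trials at a common change of 0.5 SD, against about 14% for the control arm. Alpha, correlations and effect sizes are assumptions, because the protocol gives none. The post-hoc wording is an error whatever values are assumed.

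**What to change.** For each outcome, name one between-arm model as primary. It can be a linear mixed model with arm, visit, arm-by-visit and baseline value-by-visit terms and correlated errors within participant, or ANCOVA at day 90 with the baseline value as covariate. Report the adjusted arm difference at day 90 with its 95% CI. With the mixed model, days 30 and 60 come from the same fit, and participants who miss a visit stay in the analysis without imputation.

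Label the within-arm RM-ANOVA descriptive, and state that its p-values will not support a treatment claim. Replace the post-hoc test with a named nonparametric repeated-measures test such as Friedman.

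Averaging the screening and baseline readings is optional. The screening reading is the one most exposed to practice effects and to selection on eligibility, so it need not be part of the change.

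The cost is a revised paragraph, a few lines of SPSS syntax and some added model assumptions. No new data are needed. The article reports recruitment as ongoing, so the change can be made before analysis.

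### The post-hoc fallback to RM-ANOVA is wrong as written, and the between-arm test for the clinical continuous outcomes is left to a choice made after seeing the data

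*Protocol article*

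**What the plan says.** All references are to the protocol article.

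- **Within arms** (Statistical methods): for LogMAR acuity, VFI, MD, PSD, RNFL thickness, IOP and CCT, "repeated-measures analysis of variance (RM-ANOVA) or a suitable post-hoc test will be employed to analyze continuous variables", with the choice made "depending on the normality of distribution".
- **Between arms** (Statistical methods): "Between-group comparisons will be performed using the unpaired t-test or its nonparametric alternatives as needed". No other between-arm analysis of these outcomes is given. The trigger for the switch and the form of the t-test (pooled or unequal-variance) are not stated.
- **Laboratory parameters** (Statistical methods): these "will be assessed via paired t-tests for within-group changes and unpaired t-tests for between-group differences". No switching rule applies to them.
- **Arm sizes** (Sample size): "30 participants assigned to the intervention group and 20 participants assigned to the control group".
- **Status** (Sample size): "This is an exploratory study; no prior data exists for neuroprotection as the primary outcome in POAG with Ayurveda intervention". The article states no significance level.

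**The concern.** There are two separate problems.

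First, the within-arm rule names the wrong kind of procedure. A post-hoc test locates differences after an omnibus test such as RM-ANOVA. It is not the alternative when the data are not normal. Anyone following the sentence with non-normal data has no valid analysis to run.

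Second, the between-arm comparison, which is what the Objectives call for, is not fixed. A t-test compares means and yields a mean difference. A rank test such as Mann-Whitney has a different null hypothesis and yields a different effect. Outcomes lists four primary measures (MD, PSD, VFI, RNFL thickness) and Objectives names days 30, 60 and 90, which makes 4 x 3 = 12 comparisons. Nothing stops one measure being tested by means at one visit and by ranks at the next. The choice would be made with allocation known: Blinding says the trial is open-label, and the principal investigator both assigns participants (Randomization) and enters the data (Data management).

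A further consideration is the unequal arm sizes. If the t-test is the pooled version, unequal arms make it sensitive to unequal spread.

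**Working it through.** **Inputs.** From the document: 20 control and 30 intervention participants. Assumed, because the article gives none of them: two-sided 0.05; a normality check by Shapiro-Wilk at 0.05 in each arm; pooled t-test if both arms pass, otherwise Mann-Whitney; SD ratios of 1, 1.5 and 2 in either direction. The plan has no figure of its own to reproduce.

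**Step 1: why 20 v 30 matters only when SDs differ.** Let C be the control SD and I the intervention SD.

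- True variance of the mean difference: C²/20 + I²/30.
- What the pooled t-test estimates on average: [(19C² + 29I²)/48] x (1/20 + 1/30).
- C = I = 1: both equal 0.0833, so the standard error is right.
- C = 2, I = 1: true 4/20 + 1/30 = 0.2333; pooled (105/48) x 0.0833 = 0.1823. The standard error ratio is √(0.1823/0.2333) = 0.88, which is too small, so the test rejects too often.
- C = 1, I = 2: true 1/20 + 4/30 = 0.1833; pooled (135/48) x 0.0833 = 0.2344. The ratio is √(0.2344/0.1833) = 1.13, which is too large, so the test is conservative.

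**Step 2: simulated type I error, normal data.** 10,000 trials per row; Monte Carlo SE √(0.05 x 0.95/10,000), about 0.2 points.

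| SD control : intervention | Normality check, then t or rank test | Pooled t always | Welch always |
|---|---|---|---|
| 1 : 1 | 5.2% | 5.1% | 5.1% |
| 1.5 : 1 | 7.4% | 7.2% | 5.2% |
| 2 : 1 | 8.9% | 8.5% | 5.1% |
| 1 : 1.5 | 3.8% | 3.5% | 4.9% |
| 1 : 2 | 3.3% | 2.9% | 5.0% |

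Repeat runs of the pooled t-test at a twofold ratio gave 8.7% and 9.2% (control more variable) and 2.7% (intervention more variable).

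**Step 3: non-normal data, equal SDs.** The switching rule gives 4.4% (exponential), 4.9% (lognormal) and 4.8% (t with 3 df). Neither the switching nor the 2:3 split moves the error rate materially.

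**Step 4: skewed data, equal means, unequal SDs (ratio 1.5 to 2).** The rule sends almost every comparison to Mann-Whitney, which rejects in 12% to 24% of trials (exponential) or 20% to 39% (lognormal). Welch gives 4.6% to 6.7% and 4.0% to about 9%. The Mann-Whitney figures are not pure type I errors for the mean, because in these settings the two distributions do differ. They show that the switch changes the question being tested.

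**The case against.** Several counter-arguments have force.

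- **The error rate need not be off.** A reader might infer that this plan's p-values do not carry their nominal level. The document does not support that. If the add-on does nothing, randomised arms share one distribution, SDs are equal in expectation, and the error is near 5%. Distortion needs a treatment that changes spread without changing the mean, and the article gives no SDs.
- **The likelier direction is conservative.** If a variable response to the add-on makes the intervention arm more spread out, the larger arm has the larger SD, and the pooled t-test rejects too rarely. No reason is at hand to expect the control arm to be the more variable.
- **The pooled version is read in.** The article says only that the t-test is unpaired.
- **Not every continuous outcome is affected.** Laboratory parameters have fixed t-tests, and normality is not stated as the trigger between arms, although it is the natural reading.
- **Chance switching is easy to overstate.** On normal data the check switches about 9.5% of comparisons, and 1 − (1 − 0.095)^12 = 70% for at least one of 12. That assumes independence. With assumed correlations of 0.9 to 0.95 between visits and 0.5 to 0.8 between measures, it is 51% to 59%. On normal data such a switch hardly affects the error rate.
- **The article is condensed and the trial exploratory.** The variance option, the normality criterion and the name of the rank test commonly sit in an analysis plan. The post-hoc wording may be a slip for RM-ANOVA followed by post-hoc comparisons.

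These points limit the size of the problem and stand. They do not repair the two statements in the article. One names a procedure that cannot do the job, and the other leaves the between-arm test open. An analysis plan that followed them would inherit both. Exploratory status does not remove the need for a fixed comparison, since the Conclusions of the Abstract present the trial as a possible foundation for larger ones.

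**Conclusion.** The point holds in limited form. The post-hoc clause is wrong as a rule for non-normal data, and this needs no assumption. It affects only the within-arm analysis. The between-arm comparison of the clinical continuous outcomes is not fixed in advance, so its hypothesis and effect measure can vary by measure and visit, with allocation known.

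The effect on error rates is conditional. With equal SDs there is essentially none (4.4% to 5.2% in the distributions examined). With SDs differing up to twofold at 20 v 30, a pooled t-test on normal data runs from about 3% to about 9%, depending on which arm is more variable, while Welch stays near 5%. These figures rest on an assumed two-sided 0.05 and assumed SD ratios. The figures for the switching rule also rest on an assumed Shapiro-Wilk check. The importance is minor to moderate, and the change is worth making because it is so cheap.

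**What to change.** 1. In the within-group sentence, delete the post-hoc alternative or replace it with a proper repeated-measures alternative, such as a rank-based repeated-measures test or a mixed model.
2. In the between-group sentence, delete the option of switching to nonparametric alternatives.
3. State one between-arm analysis for every clinical continuous outcome at all visits: the mean difference with 95% CI, from the unequal-variance (Welch) test or from a baseline-adjusted model with heteroscedasticity-robust standard errors. Other choices could be defended; what matters is that one is fixed in advance.
4. Name one rank-based or bootstrap sensitivity analysis, to be reported whatever the normality result.

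The cost is wording only. SPSS, the software the article names, prints the unequal-variance result by default. The downsides are a very small loss of power if the variances are equal and some loss against a rank test if the data are heavily skewed. Under extreme skew with unequal spread, Welch is not exact either (up to about 9% in the lognormal case), which is a reason to keep the sensitivity analysis.
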